## Investigational plan

### Study design and randomisation

This international, multicentre (approximately 76 sites in European Union countries), phase II study is conducted according to a double-blind, placebo-controlled, randomized (1:1 ratio, i.e. 1 Vx-001 and adjuvant vs 1 placebo and adjuvant) design.

The aim of the study is to assess the efficacy of Vx-001 vaccination as maintenance treatment in patients after 4 cycles of first-line chemotherapy treatment. Patients should have documented stage IV NSCLC as defined by IASLC Lung Cancer Staging Project (7th edition) or recurrent stage I-III disease at least 6 months after initial treatment, or after the end of adjuvant chemotherapy or after standard locoregional treatment as defined by the American College of Chest Physicians. To be eligible, patients entering the study should have documented either stable disease or objective response (PR or CR) after first line chemotherapy, will have to be HLA-A*0201 positive and their tumor will have to be TERT-positive.

Patients are administered at predefined visits the Vx-001 + Montanide ISA51 adjuvant subcutaneously, at a dose of 2mg, or placebo + Montanide ISA51 adjuvant subcutaneously. The vaccination protocol comprises of two injections with the TYR-Vx001 or placebo, one at day 0 and another at week 3, and four injections with the ARG-Vx001 or placebo, at weeks 6, 9, 12 and 15.

Following the treatment assessment at week 18, patients receive the ARG-Vx001 or placebo, every 12 weeks starting from week 27 until treatment discontinuation.

The patient may discontinue treatment for one of the following reasons:

- Progression assessed by CT scan and according to RECIST criteria,
- Adverse event, including clinical adverse event, unexpected toxicity, clinically significant biological or physical examination abnormality,
- Death, to be considered as an adverse event within 28 days following the vaccination,
- Major protocol violation,
- Withdrawal of consent,
- Other reason.

All patients withdrawn from the study for any reason must undergo a complete final study termination visit and enter in the follow-up period. If the patient discontinues the study due to a study drug-related adverse event, s/he must be followed

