The maximum duration of the treatment period for any patient for this study (comprising of the entire period of vaccinations until progression or withdrawal for any other reason) will be no more than the duration of the study. The duration of active follow up for survival and disease recurrence related to study participation will be dictated by the completion of the final analysis. Upon completion of the final analysis and if appropriate, patients under active treatment will continue to receive Vx-001 (the ARG-Vx001 peptide) within the remit of the study, until disease progression or marketing authorization of the vaccine and at the latest until the end of 2018. During this period patients will be followed-up every 12 weeks as described in the protocol. Patients under placebo treatment will stop to receive placebo and must undergo a complete final study termination visit and enter in the follow-up period for collection of survival data.

Treatment administration and duration:

- Investigational product:

Patients receive two vaccinations with 2mg TYR-Vx001 (weeks 0, 3), four vaccinations with 2mg ARG-Vx001 (weeks 6, 9, 12, 15) followed by vaccinations with 2mg ARG-Vx001 every 12 weeks commencing at week 27 until disease progression. If appropriate, patients, that have not progressed, will continue to receive Vx-001, until disease progression, unacceptable adverse events, death, major protocol violation, withdrawal of consent, or other reason as study closure.

Solutions for injection of Vx-001 peptides will be emulsified with adjuvant Montanide ISA51™ just prior to injection and will be administered subcutaneously.

- Reference therapy: Placebo:

Patients receive two subcutaneous injections with TYR-Vx001 Placebo at weeks 0, 3, followed by four vaccinations with ARG-Vx001 Placebo (weeks 6, 9, 12, 15) followed by injections of ARG-Vx001 Placebo at 12-week intervals commencing at week 27 until disease progression, unacceptable adverse events, death, major protocol violation, withdrawal of consent, or other reason as study closure, or study unblinding, if earlier.

Placebo solutions for injection will be emulsified with Montanide ISA51™ and will be administered subcutaneously.

The vaccination schedule is detailed in Figure 1.

Figure 1: Detailed schedule of vaccinations

Randomization:

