| **Time (weeks)** |  | Up to 3 weeks after last chemotherapy administration | 0 | 3 | 6 | 9 | 12 | 15 | 18 weeks | 27, 52, 75, and every 24 weeks until EOT | 39, 63 and every 24 weeks until EOT | Final visit | Survival follow-up |
| **Vaccination** |  |  | **_TYR-Vx001_** | **_TYR-Vx001_** | **_ARG-Vx001_** | **_ARG-Vx001_** | **_ARG-Vx001_** | **_ARG-Vx001_** |  | **_ARG-Vx001_** | **_ARG-Vx001_** |  |  |
| **Eligibility** | Informed consent | X | X^1^ |  |  |  |  |  |  |  |  |  |  |
|  | Inclusion/exclusion criteria | X | X |  |  |  |  |  |  |  |  |  |  |
|  | Blood sample for HLA typing | X |  |  |  |  |  |  |  |  |  |  |  |
|  | Tumour sample for TERT and biomarker | X |  |  |  |  |  |  |  |  |  |  |  |
|  | Allocation of IWRS subject number | X |  |  |  |  |  |  |  |  |  |  |  |
| **Randomization** | Randomization |  | X |  |  |  |  |  |  |  |  |  |  |
| **Study Drug** | **Vx-001 - Placebo** |  | X | X | X | X | X | X |  | X | X |  |  |
| **Safety** | Urinary pregnancy test |  | X |  |  |  |  |  |  |  |  | X^2^ |  |
|  | Demography, medical and treatment history |  | X |  |  |  |  |  |  |  |  |  |  |
|  | Physical exam, vital signs |  | X | X | X | X | X | X | X | X | X | X |  |
|  | ECOG Performance Status |  | X |  |  | X |  |  | X | X |  | X |  |
|  | Injection-site inspection |  | X | X | X | X | X | X | X | X | X | X |  |
|  | Body weight  (height at baseline) |  | X |  |  |  |  |  | X | X | X | X |  |
|  | 12-Lead ECG |  | X |  |  |  |  |  | X |  |  | X |  |
|  | Adverse Events/Toxicity assessments | X**** | X | X | X | X | X | X | X | X | X | X |  |
|  | Record concomitant medications |  | X | X | X | X | X | X | X | X | X | X |  |
|  | Haematology^3^ & clinical chemistry^4^ |  | X^6^ |  |  | X |  |  | X | X | X | X |  |
| **Efficacy** | Chest /abdomen CT or MRI | X** |  |  |  |  |  |  |  |  |  |  |  |
|  | Bone scanning^5^ | X |  |  |  |  |  |  |  |  |  |  |  |
|  | Blood sample (immunomonitoring) and biomarkers)^7^ |  | X |  | X |  |  |  | X |  | X | X^8^ |  |
| **Survival** | Record post-study treatments and responses |  |  |  |  |  |  |  |  |  |  |  | X |

.

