#### Secondary efficacy analyses

The following secondary endpoints will be analysed on the FAS and PP sets:

- Twelve months survival:

A patient overall survival (success) at 12 months is defined as a patient who is alive as confirmed by the visit at week 52. If the patient misses the visit or has been lost to follow-up, every effort will be made by the investigator to ascertain whether the patient was alive on the theoretical date of his/her week 52 visit.

A one-sided Pearson’s chi-squared test of proportions will be used to compare the survival rate of the Vx-001 treated group to the placebo treated group at 12 months (Statistical Table 22).

- Time to Treatment Failure (TTF)

Time to treatment failure is defined as the interval between the date of first study treatment and the date of early withdrawal, or the date of the initiation of other anti-tumor treatment, whichever will come first. Patients without early withdrawal or initiation of another anti-tumor treatment will be censored at their last tumor assessment of target or non-target lesions. If patient have neither any failure events nor any post-baseline tumor assessment censoring time will be set to zero.

All these secondary endpoints are "time to event" endpoints and will be analyzed via

- Kaplan-Meier curves by treatment arm and log-rank test for their comparison (Statistical Table 23, Figure 5)
- Cox regression model where the treatment effect will be included and also the stratification factors and prognostic factors specified in the section 5.2.4.2 will be also included. Via this Cox model a two-sided 95% confidence interval of the hazard ratio of the treatment effect will be provided for both population (FAS and PP sets) (Statistical Table 24, Figure 6).

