### Windows for time points

Patients have to visit the clinic/institution for investigational product administration and assessments according to the Flow Chart and Schedule of Assessments (see section 2.3.3) Permitted deviations from the predetermined dates of visit (due to weekends, public holidays etc) may be as follows:

- Screening period: can start during the first line chemotherapy and should be completed at the latest 3 weeks and 4 days after administration of the last cycle of first-line platinum-based chemotherapy,
- Baseline, randomization and first dose of vaccination: up to 4 weeks and 4 days after the last administration of the first-line chemotherapy
- Doses 2-6 of vaccination: ± 4 calendar days
- Week 18 : ± 4 calendar days
- Doses 7 to end of study vaccination: ± 14 calendar days
- End of study treatment visit: ± 4 calendar days
- Survival follow-up contact: ± 28 calendar days

Any deviations greater than the above, will be regarded as a protocol deviation. The sponsor will have to be notified, to decide whether the deviation constitutes a minor or major protocol deviation. If required, the Steering committee will be consulted. When the permitted deviations are applied, or when the study treatment has to be postponed, the next study visit should be carried out at a time that allows a minimum of 14 days between 2 vaccinations (from doses 1 to 6 of vaccination) and a minimum of 2 months between 2 vaccinations (from doses 7 to the end of study treatment). In addition, effort should be made to keep up with the schedule, based on the date of first investigational product administration (first dose).

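### Twelve-month survival is tied to a visit that may take place 14 days early, so some deaths before month 12 can count as 12-month survival; the effect is small and a fixed day from randomisation removes it

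*SAP*

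**What the plan says.** Section 5.2.4.3 (Secondary efficacy analyses) defines the endpoint by a visit: "A patient overall survival (success) at 12 months is defined as a patient who is alive as confirmed by the visit at week 52". For a patient who misses that visit or is lost to follow-up, the investigator is to "ascertain whether the patient was alive on the theoretical date of his/her week 52 visit".

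Section 5.4.3 (Windows for time points) lets the later injection visits move: "Doses 7 to end of study vaccination: ± 14 calendar days". Six injections are given by week 15, so the one-year injection is among these. Survival contacts after treatment have a window of 28 days either side.

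Overall survival itself runs from randomisation to death (5.2.4.1). Section 5.3.2 imputes missing 12-month status as death on Vx-001 and alive on placebo.

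On the schedule, section 2.3.1 gives injections "every 12 weeks starting from week 27 until treatment discontinuation" and repeats this under treatment administration: "followed by vaccinations with 2mg ARG-Vx001 every 12 weeks commencing at week 27 until disease progression". The flow chart under Study assessments and study plan has two columns for this period, headed "27, 52, 75, and every 24 weeks until EOT" and "39, 63 and every 24 weeks until EOT".

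**The concern.** A 12-month survival rate should depend only on whether the patient was alive 12 months after randomisation. Here it depends on how status was established. An attended visit settles the outcome on the day it happens, which may be two weeks early. A missed visit is settled on the theoretical date. Two patients with the same date of death can therefore be classified differently.

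This endpoint was the trial's primary endpoint before the amendment, and section 5.1.2 still gives it a one-sided test at 0.05. As written, its proportion need not agree with the 12-month Kaplan-Meier estimate from the same death dates. A Vx-001 patient seen alive on day 350 and then lost is a success under 5.2.4.3. Under a fixed-day rule the same patient would be missing and, by 5.3.2, imputed as a death.

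A second, independent matter is that the SAP gives two different weeks for the one-year injection, so the nominal date to which the window attaches is not settled.

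**Working it through.** **1. The classification rule.** Week 52 is 52 × 7 = 364 days after the first dose, which is scheduled at the same visit as randomisation. The earliest visit within the window is 364 − 14 = day 350. Take a death on day 356:
- Visit attended on day 350, patient alive: success.
- Visit missed, status taken on day 364: failure.

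The error runs one way. A patient who dies before a late visit has missed it and is judged on the theoretical date.

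**2. The schedule.** Every 12 weeks from week 27 gives 27, 39, 51, 63, 75. The flow chart gives 27, 39, 52, 63, 75, with gaps of 12, 13, 11 and 12 weeks. Only the one-year visit differs.

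**3. The SAP's own figure.** Inputs from section 2.3.3: 43% and 58% alive at 12 months, 100 evaluable patients per arm, one-sided 0.1, power about 80%. With pooled variance under the null:
- Power = Φ[(0.15 − 1.2816 × √(2 × 0.505 × 0.495 / 100)) / √((0.43 × 0.57 + 0.58 × 0.42) / 100)] = 80.2%.

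The stated 80% reproduces. At the current one-sided 0.05 level the same formula gives 68.5%.

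**4. Upper bound on misclassified deaths.** Under exponential survival, S(t) = 0.43^(t/365.25) on placebo and 0.58^(t/365.25) on Vx-001. If every patient were judged at a visit on day t, the excess over true 12-month survival is S(t) − S(365.25).

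| Day judged | Placebo | Vx-001 | Difference | Power at 0.05 |
| --- | --- | --- | --- | --- |
| 365.25 (12 months) | 43.0% | 58.0% | 15.0 | 68.5% |
| 364 (week 52) | 43.1% | 58.1% | 15.0 | 68.4% |
| 350 (week 52 less 14 days) | 44.5% | 59.3% | 14.8 | 67.5% |
| 343 (week 51 less 14 days) | 45.3% | 60.0% | 14.7 | 67.0% |

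For the week-52 anchor, which the endpoint names, the excess is 1.5 points on placebo and 1.3 on Vx-001, or 1.7 and 1.5 patients per 110. The treatment difference falls by about 0.2 points. The day-343 row is shown only as a limit: the excess is then 2.3 and 2.0 points, and the difference falls by about 0.3.

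**5. How far the bound overstates.** It places every patient at the earliest permitted day. If visits were instead spread evenly over 14 days either side of week 52 (an assumption), the average earliness is 14/4 = 3.5 days. That gives about 0.4 placebo and 0.3 Vx-001 patients per 110, even if everyone were still on treatment.

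**The case against.** The strongest reply is that the SAP already has a reference date and the intended reading is clear. The endpoint is called survival at 12 months, the sample-size section speaks of 12 months from randomisation, and counting a known earlier death as a success is the least natural reading. If baseline is numbered day 1, as in sections 2.3.4 and 5.4.1, the week 52 date is day 365. Patients off treatment have no week 52 injection visit and presumably fall under the theoretical-date rule. Those who do attend have not progressed and are less likely to die within two weeks. Section 5.3.5 makes the primary analysis the only basis for definitive conclusions.

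Most of this stands, and it limits the importance of the point. It does not remove it: the theoretical date is invoked only for a missed visit or loss to follow-up, and nothing corrects a success recorded at an early visit.

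Four stronger readings are tempting but not supported:
- *That the week 51/52 conflict causes the misclassification.* It does not. The early-visit problem follows from the window alone, and 5.2.4.3 names week 52 only, so day 343 pairs that endpoint with an anchor it does not use.
- *That the chance of dying by month 12, given alive at the earliest visit, is the misclassification rate.* It is conditional on survival to that visit and assumes that everyone is seen on that day.
- *That the arm treated longer gains.* The SAP gives no on-treatment proportion at one year, and under its survival assumptions the excess is slightly larger on placebo.
- *That the per-protocol set is affected.* A window breach is a deviation, but whether it is major is decided at blind review, against possible effect on the primary analysis.

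The schedule stands in a section of protocol highlights, and the protocol may settle the week. The SAP still contradicts itself.

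**Conclusion.** The point holds as a defect of definition with a small effect. For a week-52 anchor the inflation is at most about 1.5 points on placebo and 1.3 on Vx-001. The treatment difference changes by about 0.2 points, and by no more than about 0.3 under either anchor. These figures rest on the SAP's exponential survival, first dose on the day of randomisation, every patient judged at the earliest permitted visit, and similar attendance in both arms. If only one arm were affected, the shift could not exceed that arm's own 1.3 or 1.5 points on the week-52 anchor.

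The primary logrank analysis uses actual death dates and is unaffected. The change is still worth making, because the rule can misclassify known deaths on a formally tested secondary endpoint. The week 51/52 contradiction is real but separate, and the documents do not support a claim that it biases the result.

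**What to change.** In 5.2.4.3, replace the visit-based definition with one taken from the overall survival data at a fixed day from randomisation, for example day 365. A patient is a failure if death occurs on or before that day, and a success if known to be alive after it, regardless of visit date or treatment status. In 5.3.2, state that the worst-case imputation applies only when status at that day is unknown.

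Separately, the sponsor should reconcile the 12-week rule in sections 2.3.1 and 2.3.4 with the flow chart, so that the 14-day window in 5.4.3 has one anchor. Which week applies is for the sponsor to decide.

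The cost is a few sentences in the SAP before unblinding. Dates of death and last contact are already collected for the primary endpoint, so no new data are needed.

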### **Study treatment discontinuations - Study discontinuations**

Patients may voluntarily discontinue participation in this study at any time without giving reason(s). The investigator may also, at his/her discretion, withdraw the patient from the study at any time.

The patient may discontinue treatment for one of the following reason:

- Progression assessed by CT scan and according to RECIST criteria,
- Adverse event, including clinical adverse event, unexpected toxicity, clinically significant biological or physical exam abnormality,
- Death, to be considered as an adverse event if it occurred within 4 weeks after a vaccination,
- Major protocol violation,
- Withdrawal of consent,
- Other reason.

All patients withdrawn from the study for any reason must undergo a complete final study termination visit and enter in the follow-up period.

If the patient discontinues the study due to a study drug-related adverse event, s/he must be followed weekly until resolution or stabilization of the event, whichever occurs first.

Once the patient has discontinued the investigational treatment, the date of discontinuation and reason(s) must be documented in the patient’s medical records and eCRF. Assessments for the final visit, should be performed. Once a patient discontinues the randomized therapy, the patient will not be allowed to be retreated with study therapy. After discontinuation of the investigational product, all patients will be followed for further anti-cancer treatments and survival until death. Further treatment of the patients may continue according to institutional standard of care.

Every effort will be made by the investigator to ensure that patients who have disease progression will continue to be followed up for the evaluation of the primary endpoint, even though they are no longer receiving investigational product.

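### Time to treatment failure does not name death as an event and rests on an undefined term, so a death on study treatment can be censored instead of counted as a failure

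*SAP*

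**What the plan says.** The definition is in SAP section 5.2.4.3 (Secondary efficacy analyses): "Time to treatment failure is defined as the interval between the date of first study treatment and the date of early withdrawal". The second event is the start of another anti-tumour treatment, and the earlier of the two counts. All other patients are censored: "Patients without early withdrawal or initiation of another anti-tumor treatment will be censored at their last tumor assessment". For a patient with no failure event and no scan after baseline, the rule is that without "any post-baseline tumor assessment censoring time will be set to zero". Death appears neither as an event nor as a reason for censoring. *Early withdrawal* is not defined there, in section 3.1, or among the derived variables in section 8.

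Death does appear in the lists of reasons for discontinuing treatment. The Study design and randomisation section has "Death, to be considered as an adverse event within 28 days following the vaccination", and the discontinuation subsection of 3.1 has "Death, to be considered as an adverse event if it occurred within 4 weeks after a vaccination". That subsection also requires the date of and reasons for discontinuation to be recorded, and says: "All patients withdrawn from the study for any reason must undergo a complete final study termination visit and enter in the follow-up period".

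Section 5.3.2 sets one censoring approach for all time-to-event analyses, namely the last information available. Sections 5.1.2 and 5.3.5 make the TTF tests illustrative, at two-sided 0.05.

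**The concern.** A TTF definition has to say what happens to a patient who dies while still on study treatment. Here the answer depends on whether death falls under *early withdrawal*, and the SAP does not say. Two competent programmers could code the same patient in opposite ways.

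The literal coding is the harmful one. Death makes later withdrawal or new therapy impossible, so it is not non-informative censoring, which Kaplan-Meier, log-rank and Cox all assume. The rule also backdates the censoring to the last scan. A patient who dies before any post-baseline scan is censored at time zero, enters no risk set, and drops out of the log-rank and Cox analyses.

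TTF is one of only two secondary endpoints, with its own Kaplan-Meier curve, log-rank test and Cox model on both the FAS and PP sets. A plan meant to fix methods before unblinding should not leave its event definition to the programming stage.

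**Working it through.** **Reading the sections together.** There are two candidate readings.

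- *Death counts as early withdrawal.* In favour: death is a listed reason for discontinuing treatment; the 3.1 subsection heading covers treatment and study discontinuation together; it requires a discontinuation date; and section 5.2.2 tabulates withdrawals by reason.
- *Death is not early withdrawal and is censored.* In favour: 5.2.4.3 neither refers to that list nor uses its term (the lists speak of discontinuing treatment), and it censors everyone outside its two named events.

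The text settles on neither.

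**Size if deaths are censored.** The SAP states no TTF rate, event count or power, so there is no plan figure to reproduce. What follows is an illustration.

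Inputs from the SAP (revised sample-size section): 12-month survival of 43% (placebo) and 58% (Vx-001), exponential.

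- Death hazard, placebo: −ln(0.43)/12 = 0.0703 per month
- Death hazard, Vx-001: −ln(0.58)/12 = 0.0454 per month
- Death hazard ratio: 0.0454/0.0703 = 0.645

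Assumed, not in the SAP: a 4-month median for non-death failures, equal in both arms, so h = ln 2/4 = 0.1733 per month; and a share f of the death hazard falling on treatment before any other failure, with f = 0.1, 0.25 or 0.5.

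Six-month failure with deaths censored is 1 − exp(−6h) = 64.6% in both arms. With deaths counted it is 1 − exp(−6(h + f × death hazard)). The composite hazard ratio is (h + f × 0.0454)/(h + f × 0.0703).

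| f | Placebo, deaths counted | Vx-001, deaths counted | Understated by (points), placebo / Vx-001 | Composite HR (1.00 if deaths censored) |
| --- | --- | --- | --- | --- |
| 0.1 | 66.1% | 65.6% | 1.5 / 0.9 | 0.99 |
| 0.25 | 68.2% | 67.0% | 3.5 / 2.3 | 0.97 |
| 0.5 | 71.4% | 69.1% | 6.7 / 4.5 | 0.94 |

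At f = 0.25 the hazard ratio is (0.1733 + 0.0113)/(0.1733 + 0.0176) = 0.1846/0.1909 = 0.97. The difference between arms at 6 months is 68.2 − 67.0 = 1.2 points, against none with deaths censored.

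**Direction.** With the same f in both arms, the composite hazard ratio is a weighted average of the non-death ratio and the death ratio of 0.645. Censoring deaths leaves only the non-death ratio. If that lies above 0.645, as in the table, censoring understates the benefit. If it lies below, censoring exaggerates it. For example, with a non-death ratio of 0.50 (assumed) and f = 0.25, the composite is (0.0866 + 0.0113)/(0.1733 + 0.0176) = 0.0980/0.1909 = 0.51, and censoring deaths gives 0.50.

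Backdating to the last scan or to time zero is not modelled.

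**The case against.** The strongest reply is that a death on treatment is naturally an early withdrawal whose reason is death. The SAP lists death among the reasons for stopping, asks for a discontinuation date, and tabulates withdrawals by reason. On that reading deaths already count and only a term needs defining. The protocol, not shown here, may define it. This stands as a fair reading, and it rules out saying that the SAP censors such deaths as a matter of fact.

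A reader might also infer that sections 3.1 and 5.2.4.3 contradict each other, because a patient who has died cannot have a termination visit and enter follow-up. That goes too far. The visit sentence is general wording that follows a list including death, and it does not show that deaths are excluded. What is shown is an undefined term.

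Two further inferences fail. One is that censoring must pull the comparison towards no difference; this holds only under the equal non-death hazards assumed in the table. The other is to take all early deaths as the size of the problem. At the SAP's rates, 34% of placebo and 24% of Vx-001 patients die by month 6 (1 − exp(−6 × death hazard)). Many of them will first have stopped for progression or an adverse event, or started new therapy, and so be failures already.

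What remains is that 5.2.4.3 lists two events and censors the rest, and nothing in it tells the analyst to count a death.

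**Conclusion.** The point holds as an ambiguity with a harmful literal reading. As worded, a patient who dies on study treatment can be censored at an earlier scan or at time zero. If so, failure is understated in each arm: by 0.9 to 6.7 points at 6 months under the assumptions above. The effect on the comparison is probably small, with a composite hazard ratio of about 0.94 to 0.99 against 1.00, and it could run either way. These figures rest on exponential hazards, an assumed 4-month non-death median equal in both arms, and an assumed share of the death hazard on treatment.

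The stakes are limited: the TTF tests are illustrative and cannot rescue the study, and the primary survival analysis has death as its event. The change is still worth making, because it replaces a rule that can give a biased result with one that cannot be read two ways on this point.

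**What to change.** In section 5.2.4.3, define TTF as the time from first study injection to the earliest of:

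- permanent discontinuation of study treatment for any reason listed in 3.1;
- start of another anti-tumour treatment;
- death from any cause, using the date of death where there is no earlier discontinuation date.

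Use the same term for discontinuation in 3.1 and 5.2.4.3. In the same edit, reconcile the TTF censoring date (last tumour assessment, or time zero) with section 5.3.2, which applies the last-information-available rule to every time-to-event analysis.

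The cost is a few lines of SAP text. Death dates are already needed for the primary endpoint. Median TTF may come out slightly shorter than if deaths were censored.

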### Handling of Dropouts or Missing Data

For the primary endpoint, if no information is available on patient survival, the patient will be censored at the time of the last information available. Also, for all time-to-event analyses the same censoring approach will be used. For the 12 months survival analysis (secondary efficacy endpoint), the missing efficacy data will be imputed using the worst case approach *(i.e.* “death” for the patients randomised in the Vx-001 arm and “alive” for the patients randomised in the placebo arm).

For all other variables except missing/incomplete dates (see below), missing data will be treated as missing and no imputation will be done.

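### Time to treatment failure: the time-zero censoring rule removes only patients who have not failed, and the TTF rules conflict with the SAP's general censoring rule

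*SAP*

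**What the plan says.** SAP section 5.2.4.3 (Secondary efficacy analyses) gives this TTF definition: "the interval between the date of first study treatment and the date of early withdrawal, or the date of the initiation of other anti-tumor treatment". The earlier of the two dates counts. The section then gives two censoring rules for patients without a failure:

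- The general case: "Patients without early withdrawal or initiation of another anti-tumor treatment will be censored at their last tumor assessment of target or non-target lesions".
- The case where no scan was done after baseline, so that there is no date to use: "If patient have neither any failure events nor any post-baseline tumor assessment censoring time will be set to zero".

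Section 5.3.2 (Handling of Dropouts or Missing Data) deals first with missing survival information, where "the patient will be censored at the time of the last information available". It then extends this to other endpoints: "Also, for all time-to-event analyses the same censoring approach will be used". No exception is made for TTF.

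In the flow chart under Study assessments and study plan, the row "Chest /abdomen CT or MRI" is marked in the screening column only, and that mark carries a footnote. The same section schedules treatment visits every 3 weeks to week 15 and every 12 weeks from week 27.

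TTF is one of two secondary endpoints. Under sections 5.1.2 and 5.3.5 its tests are illustrative.

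**The concern.** Both TTF events become known through treatment visits and follow-up contacts. Neither is a reading from a scan. A censoring date tied to the last tumour assessment suits a progression endpoint. Here it sets aside failure-free time that the treatment visits have already documented.

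The two rules do different harm. Censoring at the last assessment only cuts off the time since the last scan. The time-zero rule removes the patient altogether, and it applies only to patients who have not failed, so who is removed depends on the outcome.

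The SAP also gives two answers to one question. A programmer working from section 5.2.4.3 and another working from section 5.3.2 would build different TTF datasets. At stake are the TTF medians, the failure-free rates and the hazard ratio in the TTF tables and figures.

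**Working it through.** **1. The passages side by side**

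| Failure-free patient | Section 5.2.4.3 | Section 5.3.2 |
|---|---|---|
| With a post-baseline tumour assessment | Censored at the last assessment | Censored at the last information available |
| Without one | Censored at time zero | Censored at the last information available |

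A treatment visit after the last scan is later information, so the two columns usually give different dates. This conflict needs no assumption about how often patients are scanned.

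**2. How the time-zero rule selects on outcome**

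Take two patients without a post-baseline scan. One starts another therapy: this is an event at the full observed time, and the patient is at risk until then. The other is still on treatment at the cut-off: this patient is censored at zero and is in no risk set, so adds nothing to the Kaplan-Meier, log-rank or Cox results.

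**3. Inputs**

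- From the SAP: recruitment of 39 months, and analysis when all patients have 6 months of follow-up. With uniform accrual, follow-up is uniform on 6 to 45 months (39 + 6).
- Assumed, because the SAP gives no TTF figures: exponential TTF; placebo median 3, 5 or 8 months; true HR 0.70; last scan of a scanned patient uniform over the 3 months before the cut-off.

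The SAP has no TTF figure to reproduce, so the accrual inputs were checked on overall survival. HR = ln 0.58 / ln 0.43 = 0.645. With 100 per arm there are about 142 expected deaths. Power = Φ(√(142/4) × |ln 0.645| − 1.645) ≈ 83.2%, against the stated 82.5%.

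**4. Share of patients exposed to the rules**

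With hazard λ, the share failure-free at the cut-off is (e^(−6λ) − e^(−45λ)) / (39λ).

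- Placebo median 5 months: λ = 0.693/5 = 0.1386, giving (0.4353 − 0.0020)/5.407 = 8.0%.
- Vx-001, λ = 0.70 × 0.1386 = 0.0970: (0.5586 − 0.0127)/3.785 = 14.4%.
- Placebo median 8 months: 17% and 27% by the same formula.

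**5. Effect on the hazard ratio** (Cox model, large-sample simulation, true HR 0.70)

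| Placebo median | All scanned | A quarter unscanned | Half unscanned | None scanned |
|---|---|---|---|---|
| 3 months | 0.70 | 0.71 | 0.72 | 0.74 |
| 5 months | 0.70 | 0.72 | 0.73 | 0.77 |
| 8 months | 0.70 | 0.72 | 0.74 | 0.82 |

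Repeat simulations differ by about 0.01. The ranges quoted for half unscanned (0.71 to 0.75) and none scanned (0.73 to 0.82) allow for this.

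**6. Effect on 12-month failure-free rates** (placebo / Vx-001)

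| Placebo median | True | All scanned | None scanned |
|---|---|---|---|
| 5 months | 19% / 31% | 18% / 30% | 14% / 22% |
| 8 months | 35% / 48% | 35% / 48% | 24% / 32% |

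The last-assessment rule alone barely matters when scans are recent. The bias comes from the time-zero rule.

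**7. Dependence on the exponential shape**

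Suppose instead that 20% of the Vx-001 arm never fails and hazards are otherwise equal (median 3.5 months). The event-rate ratio then moves from 0.43 to 0.44 with all scanned, 0.61 with half unscanned and 1.00 with none scanned. This is an illustration; nothing in the SAP predicts that shape.

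**The case against.** The strongest reply is that the time-zero rule may touch few patients. The SAP names CT-assessed progression under RECIST as a reason to stop treatment, continues vaccination until progression, and in the TTF rule itself presupposes post-baseline lesion assessments. The evidence for few scans is one flow-chart row whose footnote text is not in the document at hand. A reader might infer from that row that no failure-free patient is scanned and that the best-doing patients are certain to be lost. The document does not support this: the number affected cannot be read from it, and the none-scanned column is an upper bound. This part of the reply stands, which is why the result is given as a range.

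A second reply is that the specific TTF rule would override the general one. A programmer might well read it that way, but section 5.3.2 says all time-to-event analyses and excepts none, so the mismatch remains.

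A third reply is that TTF tests are illustrative and cannot rescue the study. That is correct and limits the severity.

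A reader might also infer a one-sided bias from the later stop of placebo: "Patients under placebo treatment will stop to receive placebo and must undergo a complete final study termination visit", while Vx-001 may continue. That would matter only if TTF were re-analysed at the second database lock with these stops counted as early withdrawal. The SAP announces a long-term follow-up analysis without saying that it includes TTF, and sends these patients into follow-up for survival data. It is a conditional caution only.

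Nor is death clearly missing as an event. It is a listed reason for discontinuing treatment, so naming it would be a clarification.

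**Conclusion.** The TTF censoring rules are wrong as written. They tie censoring to scans that do not define the endpoint, the time-zero rule removes patients because they have not failed, and section 5.3.2 prescribes something else. Where one arm has more non-failures, the time-zero rule pulls the HR towards 1, and it lowers the failure-free rates in any arm it affects.

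Under the assumptions above, a true HR of 0.70 is estimated at anything from 0.70 (all failure-free patients scanned within 3 months of the cut-off) to between 0.73 and 0.82 (none scanned). The SAP does not say where in that range the trial lies.

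This should be fixed, but it is not critical. It concerns an illustrative secondary endpoint, and it would be wrong to infer any effect on the primary overall survival analysis, whose censoring and power are untouched.

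**What to change.** In section 5.2.4.3, replace both TTF censoring rules with one: a patient without failure is censored at the last date known to be on study treatment and free of other anti-tumour therapy, no later than the data cut-off. Delete the last-tumour-assessment and time-zero rules. In section 5.3.2, point to this rule for TTF so that the two sections agree.

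If TTF will be re-analysed at the second lock, state that placebo stops caused by unblinding are censored at that date and not counted as failures. It would also help to say whether death on treatment counts as early withdrawal.

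The cost is SAP wording and the matching derivation, settled before the first lock. Visit and dosing dates are already collected, so no new data are needed.
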